#### **5.4. Potential risks**

The eye examination should not result in any undue discomfort. A mild stinging sensation may be experienced for a few seconds when the eye drops for refraction are instilled. The subject may also experience blurry near vision and sensitivity to bright light for about 24 hours after the instillation of eye drops. Therefore, it is suggested to wear sunglasses or a hat while going outdoors. An information sheet regarding the eye drops used in the study will be provided to participants.

The treatment interventions, specifically the spectacle, may induce blurriness, dizziness, and interrupted binocular vision at the first few days of lens wear. A one to two weeks' adaptation period may be required until the symptoms resolved. Upon experiencing persistent discomfort while wearing the spectacle, subjects or parents should report to the Investigators via phone call or message ([name] or [name], [contact]).

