### **5.9. Withdrawal criteria**

Subjects (or parents/guardians for subjects <18 years of age) are free to withdraw from participation in the study at any time upon request. No further data will be collected on subjects who withdraw from this study.

If significant intolerance to the treatment intervention is suspected at any time after randomisation, subjects can choose to withdraw or terminate treatment (either treatment or control group).

An Investigator may discontinue or withdraw a subject from the study for the following reasons:

- Significant study intervention noncompliance: unable to contact via 3 phone calls and 3 messages, more than 3 attempts to arrange missed follow-up appointments, wearing the spectacles less than 5 days a week and/or an average of less than 5 hours/day.
- If any clinical adverse event or situation occurs (e.g., allergies to eye drops, reduction of visual function such as diplopia, reduction of BCVA; subject to clinicians' judgement) such that continued participation in the study would not be in the best interest of the subject.

- If the participant meets an exclusion criterion (either newly developed or not previously recognized) that precludes further study participation.

Should subjects require discontinuation of treatment intervention for any reason, follow-up visits and data collection will not continue as scheduled. The reason for discontinuation or withdrawal from the study will be recorded on the Discontinuation/Withdrawal Case Report Form (CRF) in a web-based secure remote electronic database named Research Electronic Data Capture (REDCap). Subjects who signed the informed consent form and were Randomised but did not receive treatment intervention may be replaced. If there are subjects who signed the informed consent form, were Randomised, received the study intervention but were discontinued or withdrawn within the first month due to not meeting inclusion criteria (e.g., unable to tolerate spectacles or eye drops), and it is still within the recruitment period, then these participants' randomisation will be discarded and replaced with a participant from the next allocation. All spectacles (used or unused) will be returned to the unmasked Investigator upon withdrawal or discontinuation from the study.

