### 6.2. Statistical analysis

Data from the right eyes will be used for analyses when both eyes show fast progression. If only one eye demonstrated fast progression, that specific eye would be used for analyses. Demographic and optometric data will be displayed as mean and standard deviation, or number and percentage as appropriate. The Chi-square test (or if appropriate, Fisher's Exact test) and unpaired t-test will be performed to compare baseline between-group differences in demographics (age, sex). Myopia progression will be calculated as the difference between SER and AL at the baseline, the 6-month and the 1-year visits, respectively.

The unpaired t-test will be used to compare the changes in primary and secondary outcomes between groups. The efficacy of myopia control of DIMS lens will be determined by dividing the difference in myopia progression (or axial elongation) between two groups with the myopia progression (or axial elongation) in the SV group, then multiplied by 100%. Multiple regression analysis will be employed to identify factors that may be associated with myopia control efficacy. Regarding visual performance and comfort, subjective ratings collected by questionnaires will be compared between groups using Mann-Whitney U test.

Treatment will be discontinued if any treatment-related adverse event arises, such as constant visual disturbance (e.g., ghosting, diplopia, glare, etc.). The number of subjects

discontinuing treatment prematurely for any reason will be summarised by reasons for discontinuation. The incidence of all serious adverse events will be summarised.

Data analysis will follow an intention-to-treat approach. Missing values of outcome variables and covariates will be replaced using multiple imputation procedures with 10 sets of imputations assuming missing at random. All analyses will be 2-tailed with a significance level of 2.5%.

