### 8.3. Responsibility

In accordance the guideline for good clinical practice (GCP) by the International Council for Harmonization of Technical Requirements for Pharmaceuticals for Human Use (ICH), the Investigator/institution should ensure that adequate medical care is provided to a subject for any adverse events, including clinically significant laboratory values, related to the trial. The Investigator/institution should inform a subject when medical care is needed for an intercurrent illness of which the Investigator becomes aware. The unmarked Investigator and the PI need to evaluate the AE severity as well as the relatedness to the study procedures and study device.

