### **8.5. Documentation and follow-up**

At each study visit, the Investigator or designee will inquire about the occurrence of AEs/SAEs since the last visit. Any AE observed by the Investigator or reported by the subjects will be documented on an adverse event form onto REDCap as soon as possible after notification of the event. However, not all AEs require reporting, as they might not directly impact participant risk. Information to be collected includes event description, time of onset, clinician's assessment of severity, relationship to study product (assessed only by those with the training and authority to make a diagnosis), and time of resolution/stabilization of the event. All AEs occurring while on study must be documented appropriately regardless of relationship. All AEs will be followed to adequate resolution. An appointment will be arranged for 1-4 weeks following AE resolution to check for any recurrence or changes because of the AE. Changes in the severity of an AE will be documented to allow an assessment of the duration of the event at each level of severity to be performed. AEs characterized as intermittent require documentation of onset and duration of each episode. These will be followed-up and assessed by medically fit clinician. It will be left to the judgement of the research team to decide whether an AE is of sufficient severity to require discontinuing the participant from the study. A subject may also voluntarily withdraw from participating in the study due to what he or she perceives as an intolerable AE. If either of these occurs, the subject must undergo follow-up visits for trial assessment and be given appropriate care under medical supervision until symptoms cease, or the condition becomes stable.

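### Section 6.2 makes stopping the lenses mandatory for any treatment-related adverse event, while 5.9 and 8.5 leave it to judgement and disagree on whether follow-up continues afterwards

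*Protocol*

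**What the plan says.** The protocol speaks about stopping the study lenses in several places.

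- **6.2 Statistical analysis:** "Treatment will be discontinued if any treatment-related adverse event arises, such as constant visual disturbance (e.g., ghosting, diplopia, glare, etc". The parallel statistical text in the Overview (Section 1) does not carry this sentence.
- **5.9 Withdrawal criteria:** on suspected intolerance, "subjects can choose to withdraw or terminate treatment (either treatment or control group". Separately, "An Investigator may discontinue or withdraw a subject from the study for the following reasons"; one listed reason is a clinical adverse event such as diplopia or reduced best-corrected acuity, "subject to clinicians' judgement".
- **8.5 Documentation and follow-up:** "It will be left to the judgement of the research team to decide whether an AE is of sufficient severity to require discontinuing the participant".
- **5.4 Potential risks:** the spectacles "may induce blurriness, dizziness, and interrupted binocular vision at the first few days of lens wear", and a one- to two-week "adaptation period may be required until the symptoms resolved". Families are asked to report discomfort that persists.
- **8.3 Responsibility:** the PI and an Investigator described as unmarked (apparently a misprint for unmasked) "need to evaluate the AE severity as well as the relatedness to the study procedures and study device".

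On what happens next, 5.9 halts scheduled visits and data collection once treatment is discontinued, whatever the reason. Section 8.5 obliges a child discontinued for an adverse event to attend visits for trial assessment. Section 6.2 plans an intention-to-treat analysis with ten multiple imputations assuming missing at random.

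**The concern.** A rule that says treatment will stop, and rules that say it may stop on judgement, cannot all be followed for the same event. Section 5.18 classes any unapproved departure from the protocol as a violation, so a clinician who uses the discretion in 5.9 or 8.5 for a related event departs from 6.2.

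This reaches the primary comparison because of what stopping entails. If stopping treatment ends outcome collection, the stopping rule is also a missing-data rule for the 12-month change in spherical equivalent refraction (SER). Where that rule is applied unevenly, the missing values arise unevenly, and imputing them as missing at random may not be justified. The planned table of discontinuations by reason would also mix compulsory and discretionary stops.

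**Working it through.** The point is textual, so the first step sets the sections side by side.

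| Question | 6.2 | 5.9 | 8.5 |
|---|---|---|---|
| Trigger | Any treatment-related event | Intolerance, or an adverse event making participation not in the child's interest | An event judged severe enough |
| Force | Mandatory | Optional (child chooses, Investigator may) | Research team's judgement |
| Visits afterwards | Not stated | Not continued as scheduled | Required for trial assessment |

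**Test case: a mild, related event.** Section 8.2.1 defines related by timing and the absence of another reasonable cause, with no severity or duration threshold. Section 8.2.2 has a mild grade for events needing little or no treatment. Such an event meets the 6.2 trigger, so treatment must stop. Under 5.9 and 8.5 it need not. The instructions are incompatible.

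**Adaptation symptoms.** Section 5.4 expects early symptoms that resolve. The only illustration in 6.2 is a constant disturbance, but it illustrates a rule covering any related event. The text does not settle whether transient symptoms trigger the rule.

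**Route to the primary outcome.** A related event may or may not lead to stopping, depending on the section applied. After stopping, outcome collection may or may not continue, again depending on the section. Any missing 12-month SER is imputed as missing at random (6.2). Relatedness is judged partly by staff who apparently know the lens; under 5.6.1 unmasked Investigators dispense the lenses. Stopping could therefore depend on the arm.

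**Context: the plan's sample size.** A two-sample t-test at effect size 0.658 and 90% power gives 49.5, so 50 per group, at two-sided alpha 0.05, and 58.6, so 59, at 0.025. Both match Section 6.1. Inflation gives 59 / 0.9 = 65.6, so 66, against the stated 65, a difference of one child. The allowance is 65 − 59 = 6 per group.

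**Illustration of power.** The documents give no event or stopping rate, so the losses here are assumptions. Inputs are a difference of 0.315 D, SD 0.475 D, two-sided alpha 0.025 (z = 2.241), 65 per arm and 10% lost on single vision (SV).

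Power = Φ(0.315 / (0.475 × √(1/n_SV + 1/n_D2)) − 2.241), with n_SV = 65 × 0.9 = 58.5.

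| Assumed D2 loss | n_D2 retained | Power |
|---|---|---|
| 10% | 58.5 | 91% |
| 20% | 52.0 | 89% |
| 30% | 45.5 | 87% |

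**Illustration of bias.** If a fraction p of an arm is lost, and those lost differ by d from those retained, the retained mean differs from the full-arm mean by p × d. Taking d equal in size to the design difference, 0.315 D (an assumption), gives 0.10 × 0.315 = 0.03 D, 0.20 × 0.315 = 0.06 D and 0.30 × 0.315 = 0.09 D. The sign is unknown. Similar losses in the other arm would offset it, and imputation that uses 6-month data could recover part of it.

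**The case against.** Several points on the other side have weight.

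- **Constant as a limit.** One could read 5.4 and 6.2 together: early symptoms mean adaptation, persistent ones a report, constant related ones a stop. A reader might infer that mild blur in the first week must end treatment. That is the weakest case, and the text does not establish it. The illustration does not narrow the rule, however, so ambiguity remains, and the conflict with 5.9 and 8.5 does not rest on adaptation symptoms.
- **More stopping in the DIMS arms.** A reader might infer this because some relatedness raters know the lens. No section supports it: 5.4 does not separate the arms, 5.9 applies its intolerance rule to treatment and control alike, and no rates are given. Only possible dependence on the arm can be stated.
- **The dropout allowance would be exhausted.** Ten percent of 65 is 6.5, about the allowance of 6, but that rate is assumed. Section 5.9 also lets some children who stop in the first month be replaced while recruitment is open. The illustrated power loss is modest.
- **Treatment versus study.** Section 6.2 concerns stopping treatment; 8.5 concerns leaving the study. This softens the conflict, but 5.9 ties the two by halting scheduled data collection once treatment stops.
- **Safety visits only.** The visits in 8.5 might be meant only to follow the event to resolution. That is possible, but the section describes them as serving trial assessment and does not say so.
- **Existing safeguards.** There is one site, and 5.9 already records a reason for discontinuation on a dedicated form. Both limit the damage. Neither says which rule applied.

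**Conclusion.** The contradiction stands. Section 6.2 mandates stopping for any related event, 5.9 and 8.5 make it discretionary, and 5.9 and 8.5 disagree on follow-up afterwards. Whether the adaptation symptoms in 5.4 fall under 6.2 is unclear.

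This is more than wording, because stopping treatment can end collection of the primary outcome and the gap is then filled under missing at random. The likely harm is inconsistent and possibly non-random missing data for 12-month SER. Its direction cannot be stated, and its size cannot be derived from the documents. On assumed D2 losses of 10% to 30% against 10% on SV, power moves only from about 91% to 87%, so lost power is not the main issue. The role of unmasked staff rests on reading the description in 8.3 as a misprint.

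**What to change.** The sponsor and clinicians should reconcile 5.4, 5.9, 6.2 and 8.5 into one discontinuation rule. Its clinical content is theirs to decide, but the text should settle:

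1. whether stopping is mandatory or by judgement, and for which events;
2. whether the adaptation symptoms described in 5.4 count;
3. whether outcome data are collected after treatment stops, so that 5.9 and 8.5 agree and the intention-to-treat and imputation statements in 6.2 fit the answer.

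Section 6.2 should cross-refer to that rule. The rule should apply identically in all three groups, and the criterion met should be recorded on the Discontinuation/Withdrawal CRF. The description of the assessor in 8.3 should be clarified at the same time.

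The cost is protocol wording and one CRF field.

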### *Primary safety outcome*

- Adverse events, including biomicroscopic findings, for the treatment and control groups over 2 years

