#### **5.5. Benefits**

The refractive status and eye health conditions of the participants will be closely monitored by eye care professionals throughout the 2-year study period. The treatment interventions may slow down the myopia progression of the participants. Participants and parents do not need to pay for eye examinations or spectacles.

This research study aims to demonstrate the safety and efficacy of new spectacle lenses in reducing myopia progression in children. A positive outcome is likely to accelerate the global commercialization of this clinical management option, thereby reducing the enormous socioeconomic burden associated with vision loss due to myopia and high myopia.

To express gratitude to the participants and parents for their valuable time and contribution to the research study, they will receive either a pair of single vision spectacles or MiyoSmart spectacles upon completion of the study.

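### The safety analysis stated in Section 6.2 is narrower than the protocol's own primary safety outcome: non-serious adverse events that do not stop treatment, and biomicroscopic findings, have no stated summary by group

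*Protocol*

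**What the plan says.** **The outcome.** Section 1 (Overview, Primary safety outcome) names one primary safety outcome: "Adverse events, including biomicroscopic findings, for the treatment and control groups over 2 years".

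**The analysis.** Section 6.2 contains two safety summaries. One counts subjects "discontinuing treatment prematurely for any reason will be summarised by reasons for discontinuation". The other is "The incidence of all serious adverse events will be summarised". Neither sentence mentions group. The statistical methods in the Section 1 overview state no safety analysis.

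**The data.** Section 5.14 has adverse events and their relation to treatment collected at every time point. Section 8.2.2 has severity and relatedness recorded, and Section 8.5 requires every adverse event to be documented whatever its cause. Section 5.16 schedules an anterior ocular health examination at baseline and at each 6-monthly visit to month 24.

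**The named risks.** Section 5.4 says that the spectacles "may induce blurriness, dizziness, and interrupted binocular vision at the first few days of lens wear". Section 8.2.1 adds diplopia, ghosting, glare and eye strain to the events to be noted.

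**Stopping treatment.** Section 6.2: "Treatment will be discontinued if any treatment-related adverse event arises, such as constant visual disturbance". Section 8.5: "It will be left to the judgement of the research team to decide whether an AE is of sufficient severity to require discontinuing".

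**The concern.** A declared primary outcome should have an analysis that reports it. Here the analysis section fixes a summary that covers only part of the outcome, and the part left out is where effects of a spectacle lens are most likely to appear. Transient blur, dizziness or eye strain would not ordinarily meet the seriousness list in Section 8.1.2, which covers death, threat to life, hospitalisation, lasting disability, congenital anomaly, or a condition that investigators judge to be a significant hazard.

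The protocol also sets safety as an aim: "This research study aims to demonstrate the safety and efficacy of new spectacle lenses in reducing myopia progression in children". A statement about the safety of D2 that rested on Section 6.2 alone would not be supported by the outcome the protocol chose for that purpose.

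**Working it through.** The protocol gives no figure for this point, so the check sets its sections side by side.

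**Step 1. Does each part of the primary safety outcome reach a stated safety summary?**

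| Part of the outcome | Collected? | Safety summary stated in 6.2? |
|---|---|---|
| Serious adverse events | Yes (5.14, 8.2.2, 8.5) | Yes, incidence |
| Non-serious events that end treatment | Yes | Yes, through discontinuations by reason |
| Non-serious events that do not end treatment | Yes, with severity and relatedness | None |
| Biomicroscopic findings | Yes (5.11, 5.16) | None |

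Two of the four rows have no stated safety summary. The two that have one are not said to be broken down by group.

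**Step 2. How much does the discontinuation route catch?** Section 6.2 says that a treatment-related event leads to discontinuation. If it is applied literally, related ghosting, diplopia and glare reach the table of reasons. Section 8.5 leaves that decision to the research team. The two sections disagree, so the share of related events that reaches the table cannot be predicted from the document. Three further points limit the route under either reading:

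- Section 8.2.1 counts an event as related only if no other cause can reasonably explain it.
- Section 5.4 expects early lens symptoms to settle within one to two weeks. Children who adapt and go on wearing the lens enter no discontinuation count.
- Section 5.9 allows some children withdrawn in the first month, with intolerance of the spectacles given as an example, to have their randomisation discarded and be replaced. Early intolerance may therefore not be shown against the arm in which it arose.

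**Step 3. What does the questionnaire add?** Section 6.2 compares visual performance and comfort ratings between groups by Mann-Whitney test. Section 5.14 collects them 1 month after dispensing and 1 month after the control group's crossover. This bears on the same symptoms, but it is a rating at fixed times and not a count of events, and the protocol does not label it as safety.

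**Step 4. Scale, on assumed rates.** The protocol gives no expected adverse event rate. Take 65 children per group (Section 6.1) and an assumed proportion p with a non-serious event and no discontinuation. The expected number in neither stated safety summary is 65 × p:

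- p = 5%: 65 × 0.05 = 3.25, about 3 children
- p = 10%: 65 × 0.10 = 6.5, about 7
- p = 20%: 65 × 0.20 = 13
- p = 30%: 65 × 0.30 = 19.5, about 20

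These numbers show scale only and are not estimates for this trial.

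**Step 5. Which lens?** The outcome runs 2 years, but Section 5.6.1 moves the control group to D2 at 12 months. A 2-year tabulation by assigned group would put D2 events in the control column. Section 5.15 adds two details: first dispensing is targeted at day 30 and the crossover dispensing at day 390. Controls therefore still wear single vision lenses for about a month after the 12-month visit (390 − 360 = 30 days), and no child wears a study lens before first dispensing. A summary by group needs a rule for this.

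**The case against.** The strongest reply has three parts.

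1. **The named lens risks are not wholly lost.** A reader might infer that they vanish from the results, or would be seen only if a child stopped treatment. The document does not support that. Section 6.2 itself makes treatment-related disturbance a trigger for discontinuation and tabulates the reasons, and it compares comfort and visual performance ratings between groups. This stands, and the point is limited accordingly.

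2. **Section 6.2 does not say that these are the only summaries.** Full adverse event tables are commonly left to a statistical analysis plan, which is not at hand and may contain them. This stands in part. The absence of table layouts from a protocol would be no finding. But the protocol is not silent: it selects serious events for summary where its own outcome is all adverse events. A plan that followed Section 6.2 closely would carry the gap forward.

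3. **Section 6.2 displays optometric data as number and percentage where appropriate, which might stretch to slit-lamp findings.** It might, but the sentence names neither biomicroscopy nor adverse events and is not tied to the safety outcome.

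It is also fair to say that no data are lost and that the efficacy inference is untouched.

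**Conclusion.** The concern holds as a mismatch between the declared primary safety outcome and the stated analysis. Two components, non-serious events that do not end treatment and biomicroscopic findings, have no stated summary by group. The effect is on reporting only: collection, follow-up of events and the primary efficacy comparison are unaffected.

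Its numerical size cannot be derived from the protocol, and the 3 to 20 children per group above rests wholly on assumed rates. The conclusion also assumes that Section 6.2 is followed as written; an unseen analysis plan could already close the gap. The conflict between Sections 6.2 and 8.5 on stopping treatment is a separate inconsistency that decides how much the discontinuation table captures. The passages must be reconciled; which rule is right is not a matter for this review.

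The point is worth correcting because it concerns an outcome labelled primary and the repair is nearly free.

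**What to change.** Replace the serious adverse event sentence in Section 6.2 with:

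> The number and percentage of children with any AE, any ADE, any SAE and any SADE (by severity and relatedness), and with biomicroscopic findings by visit, will be summarised by the lens worn at onset, with months 0-12 (randomised comparison) shown separately from months 12-24 (after the control group's crossover to D2).

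Add a note that events before first dispensing are listed apart, since no study lens is yet worn. Keep the discontinuation summary, give it by group, and state whether children replaced under Section 5.9 are counted in it. Reconcile the discontinuation statements in Sections 6.2 and 8.5 so that the table of reasons has a defined meaning.

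The cost is an amended sentence, a reconciliation of existing text and a few extra tables from data already collected. No new visit, measurement or sample size is needed.
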